### Sampling method

Simple random sampling will be used for the selection of participants. Two schools will be assigned the intervention group, and two schools the control group, followed by the selection of classes. With this form of probability sampling, researchers use a sampling frame, which includes a list of all students from the selected schools. For this study, a table of random numbers, will be used for the selection of participants, up to the point the sample size is attained. The random selection of participants is achieved by way of Excel software.

### Data collection

#### Cluster randomized trial flow

*Recruitment of participants*. The teachers and principals will be updated on the study objectives, and the student eligibility criteria, for the cluster randomised controlled trial (RCT). The selection of participants will be conducted at the selected schools. Only those who are available, during the accumulation of data, will be further briefed and assessed on their eligibility, according to the inclusion and exclusion criteria, stated in a screening form. The school administration will forward an invitation, to the parents of eligible participants, to obtain written consent, before the commencement of the study. On receipt of the written consent from students and their parents, the collection of baseline data will begin. The participant information sheet, in English and Arabic, will be made available to eligible students and their parents. The participants will be provided with an explanation, on the objectives and protocols of the study. All participants involved in this study are volunteers, and guaranteed the unrestricted right, to pull out of this study, at any time. Participants will be assured, that all information related to their identities, will be kept confidential. The random selection and allocation of participants, to the intervention or control groups, will be realized through the Excel software. Subsequently, the intervention group will be subjected to the educational intervention. For the post-intervention and follow‐up assessments, the participants will be required to fill in the same questionnaire, albeit, excluding the section referring to personal information.

*Study principles*. This investigation is based on the study protocol item, recommendations for interventional trials (SPIRIT), 2013, statement [23], while complying with the consolidated standards of reporting trials (CONSORTs), statement [30]. The flowchart for the CONSORTs is displayed in Fig 2. CONSORT was developed by a group of researchers not only to identify problems associated with RCTs, but also to present the results of the research in a clear and concise manner, facilitating the reading and assessment of RCTs [30]. The CONSORT 2010 guideline were chosen because it is intended to improve the reporting of parallel- group randomized controlled trials. It enables better understanding of a trial design, conduct, analysis, interpretation and assessment of the validity of its results.

**Fig 2 pone.0289937.g002:**
[figure not shown]
Consort 2010 flow diagram.

*Randomization*. Randomization is ensured throughout the study, using sealed opaque envelopes. An independent researcher places envelopes enclosing the names of the schools in a box, and randomly selects four envelopes to represent the intervention and control schools. The independent researcher uses Excel software, for the selection of the participants. For this selection process, the IDs of all students will be entered into the datasheet, a random column will be created, and the formula " = RAND()" will be applied. Respondents will be assigned a unique code, for the allocation of a concealment mechanism. This is to circumvent individual-level bias.

*Intervention*. ‘Healthy lifestyle’ intervention is based on the HBM theory, which considers the attitudes and beliefs of adolescents, for the development of their skills and favourable behaviours. A team of health promotion experts, from the University of Malaya’s department of social and preventive medicine, with a special interest in obesity-related behaviour alteration, will assist the researcher, during the designing of the educational health promotion program.

The intervention is specifically designed to:

Provide adolescents with the facts, statistics, and harmful effects, linked to obesity and overweightness.Encourage the consumption of healthy diets, to keep the risks of obesity at bay.Promote the indulgence in physical activity, to reduce the risks of obesity.Inspire students to adopt positive health behaviours.Develop a good decision-making and self-care attitude.Develop the three health belief elements of perceived susceptibility, perceived threat, and perceived benefit vs. barriers.

The improvement in knowledge and perceived disease risk, achieved through the educational programme, will lead to a better lifestyle, in terms of a healthier eating habit, and increased physical activity. It is anticipated, that the educational programme, will serve to promote the choice of healthy food, and the engagement in regular physical activity, among adolescents in their daily lives. The intervention will be carried out in a single-blind trial. While the researchers are knowledgeable regarding the details of the intervention, the adolescents will be kept in the dark regarding the existence of the control group, and the fact that they are about to be re-evaluated. The intervention process will include the distribution of educational booklets, as well as the running of educational classes.

The educational booklets, which will be distributed to participants, in the first session, are to be taken home and read, within a period of one week. The contents of the booklets include information on the risk factors associated to NCD, and the benefits to be gained from a healthy lifestyle and appropriate physical activity.

The educational classes, which include six weekly teaching units, are aimed at curbing obesity among the students, by equipping them with relevant knowledge, and behavioural skills. The separation of students, into groups of ten, is followed by the presentation of the training units by the researcher. For each 45-minute session, 15 minutes is set aside for the presentation of the topic through PowerPoint slides, 15 minutes for group discussions, and 15 minutes for group activities. The focus of the first and second training units, will be on educating the students, regarding the perils and complications, associated to being overweight or obese. The emphasis of the first session activity, will be on the measuring of the BMI, while the emphasis of the second session activity, will be on comprehending the nutritional information provided on food labels. The third teaching unit will emphasise on the selection of a healthy diet, which includes an appropriate type and amount of food. The third session activity will entail the preparation of a healthy serving of oatmeal. The fourth teaching unit will focus on education related to physical activities, including the appropriate type, duration, frequency, and intensity of physical activity. The fourth session activity will entail a 15-minute walk, within the school playground. The fifth teaching unit involves a discussion, on the benefits and barriers associated to a healthy diet, and a fitness-promoting physical activity program. The session activity comes in the form of a role-playing exercise. For the sixth training unit, methods will be proposed for reducing the perceived barriers, enhancing adherence confidence, and improving of decision-making skills. The session activity will involve the selection of a healthy snack from a basket (decision-making skill). It is anticipated that with the proposed intervention, the participants will develop the practice of self-care, in the form of daily exercise and a healthy diet. This will go a long way towards the promotion of a healthy lifestyle, and the deterrence of obesity, among adolescents (Table 1).

**Table 1 pone.0289937.t001:** Overview of the educational intervention classes to preventing obesity.

Sessions	Topics	Area of target	Intervention
Overweight and obesity	The dangers and complications of overweight and obesity	Knowledge of overweight and obesity	PowerPoint presentation, booklet, small group discussion
Reading the nutritional fact on the food label	To learn how to read and interpret food labels	What is a serving size and serving per container	PowerPoint presentation, booklet, Various packaged foods with food labels, Videos
Healthy diet	To understand food based approaches to reduce or prevent overweight and obesity	Knowledge of type and the amount of food Choosing the healthy snack from the basket (decision-making).	PowerPoint presentation, booklet
Basics of physical activity	The physical activity types and recommended duration. Benefits of physical activity Physical activity opportunities.	To understand the importance of regular physical activity	PowerPoint presentation, booklet, Videos and workshops
Benefits and barriers of a healthy diet and physical activity program	Benefits of diet and physical activity Barriers to adherence diet and physical activity participation	Belief in diet and physical activity adherence	PowerPoint presentation, booklet, Videos and workshops
Proposed methods to decrease Perceived barriers, and Enhance confidence and Decision-making skill.	To decrease perceived barriers and enhance confidence in adherence and decision-making skill	To motivate and increase an individual’s confidence to take action to improve their healthy lifestyle	PowerPoint presentation, booklet, small group discussion

Participants will receive motivational messages via WhatsApp during the follow-up. The messages in the form of short videos, pictures and flyers will be designed to deliver information on the risk factors associated to NCD, and the benefits to be gained from a healthy lifestyle and appropriate physical activity.

### Study outcomes

#### Primary outcome

The knowledge, attitude, and practice of nutrition and physical activity questionnaire (KAP-Q) will be used, to measure the primary outcome of interest for this study, in accordance with the approach employed by Sharif Ishak et al. [31] and Harake et al. [32]. The questionnaire consists of 73 items: knowledge (30), attitude (22), and practice (21). The knowledge section serves to determine the participants’ level of comprehension, regarding nutrition and physical activity. The response options to the multiple-choice questions in the questionnaire are ‘True’, ‘False’ and ‘I do not know’. Correct responses will be designated ‘1’, while incorrect and ‘I do not know’ responses will be designated ‘0’. The maximum score is 30, and the minimum 0. A score above the mean is an indication of good knowledge. The five Likert scale responses for assessing attitude are ‘strongly agree’, ‘agree’ ‘neutral’, ‘disagree’, and ‘strongly disagree’. Eleven negatively termed questions will be inversely recoded during data analysis. The maximum score is 110, and the minimum 22. A higher score is an indication of a greater positive attitude. The practice section includes 21 questions, which come with five Likert scale responses: ‘very frequently’, ‘often’, ‘sometimes’, ‘rarely’, and ‘never’. Nine negatively termed questions will be inversely recoded during data analysis. The maximum score is 105, and the minimum 21. A higher score is an indication of a more positive practice.

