**Methods and anticipated results:**

A cluster randomized controlled study will be conducted, involving 250 Middle Eastern adolescents, in Arabic schools in Malaysia. The participants will be randomly assigned to the intervention and control groups. While the intervention group participates in six weeks of fortnightly six sessions (45 minutes per session), the control group will carry on with their regular curriculums, and normal physical activity routines. The variables which will be evaluated include anthropometric measurements, knowledge, attitude, daily routines, physical activity, sedentary behaviour, food assessment, eating attitudes test-26, and a structured questionnaire based on the HBM. Data will be collected from the intervention and control groups at baseline, post-intervention, and two months following the intervention. Data analysis will be performed by way of the SPSS Statistics software version 26. The generalized estimating equation (GEE) will be used, to test the effect of the intervention program, with regards to the selected variables (outcomes), between and within-group at baseline, as well as six weeks and two months following intervention, after adjusting for clustering. Outcomes will be assessed at each time point, along with a derived average over all three-time points; thus, ensuring that both the cumulative and overall effects are determined.

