### Statistical analysis

Data analysis will be conducted using the statistical package for social sciences (SPSS) software version 26 for Microsoft Windows (Chicago, IL, USA). An inspection for omitted values and outliers will be conducted prior to data analysis. Descriptive statistics will be applied for the presentation of the data to determine means, median, standard deviations (continuous variables), frequencies, and percentages, to represent categorical data (categorical variables). The normality of variables will be described among continuous data by way of the Kolmogorov- Smirnov test, as well as the Skewness & Kurtosis test. In the Kolmogorov- Smirnov test, a P-value > 0.05 is an indication of normal data distribution. Data not normally distributed, will be transformed into a categorical variable. In the Skewness & Kurtosis test, -1.96 to +1.96 is deemed normal data.

One Way ANOVA will be used, to determine whether any significant within-group variances occurred over time, for the selected variables, if the data is normally distributed, while Friedman’s test will be used, to determine whether any significant within-group variances occurred over time, for the selected variables, if the data is not normally distributed.

The generalized estimating equation (GEE) will be used, to test the effect of the nutrition intervention program, on the selected variables (outcomes), between & within the group, at baseline, six weeks, and two months following intervention, which is adjusted for clustering. Missing data will not be replaced. Outcomes will be assessed at each time point, along with derived average overall three-time points, thus ensuring the delivery of both the cumulative and overall effects.

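### The primary outcome is an instrument with three separate scores, assessed at each time and as an average, and no score or time is singled out as primary

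*Protocol article*

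**What the plan says.** The Primary outcome section of the protocol article uses KAP-Q "to measure the primary outcome of interest for this study", in the singular, and then divides it: "The questionnaire consists of 73 items: knowledge (30), attitude (22), and practice (21". The three sections are scored on separate ranges: knowledge ("The maximum score is 30, and the minimum 0"), attitude ("The maximum score is 110, and the minimum 22") and practice ("The maximum score is 105, and the minimum 21"). No combined score is defined, and neither a lead section nor a primary time is named.

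The Statistical analysis section applies generalized estimating equations (GEE) to the outcomes "at baseline, six weeks, and two months following intervention, which is adjusted for clustering". It adds: "Outcomes will be assessed at each time point, along with derived average overall three-time points". The Abstract says the same: "Outcomes will be assessed at each time point, along with a derived average over all three-time points".

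Nothing elsewhere settles which contrast is primary. The Sample size section works from the proportion overweight, not from a KAP score. The hypothesis in the Discussion lists knowledge, attitudes and practices together without saying whether one or all must improve.

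**The concern.** A primary outcome should fix one question: which variable, at which time, compared how. Here the section names an instrument that yields three variables, and the analysis section gives each of them several contrasts of equal standing. Counting the between-group contrasts at the two post-baseline times and the average gives 3 scores × 3 = 9.

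Two things are at stake. First, if any favourable contrast may carry the primary claim, the chance of a false claim exceeds the nominal 5%. Second, one of the candidates is a poor primary measure: the average over all three times includes baseline, when the programme cannot yet have had an effect.

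**Working it through.** **The plan's own figure.** The article states no family-wise error rate, so there is none to reproduce. Its 95% confidence level and 80% power appear only in the Sample size section, in a calculation for overweight.

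**Inputs from the document.** Three KAP scores; two post-baseline times; an average over baseline and both post-baseline times.

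**Assumptions, not in the document.** Each test is two-sided at 0.05 and unadjusted; any one significant contrast counts as primary success; every null hypothesis is true; each GEE test holds its own 5%. The between-score correlation is varied from 0 to 0.8 and the between-time correlation from 0 to 0.9.

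**Independent tests, 1 − 0.95^k.**
- k = 3: 1 − 0.95³ = 14.3%
- k = 6: 1 − 0.95⁶ = 26.5%
- k = 9: 1 − 0.95⁹ = 37.0%. This is too high for the present case, because each average is built from the same data as the single-time contrasts.

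**Correlated tests.** Multivariate normal simulation of the between-group test statistics, 400,000 draws per setting, Monte Carlo standard error about 0.1 percentage point. The nine-contrast column counts each score at the two post-baseline times and as the average over all three times. The last column counts the three scores at one time.

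| Between scores | Between times | Any of nine | Any of three |
|---|---|---|---|
| 0 | 0 | 33.1% | 14.3% |
| 0.3 | 0.5 | 26.7% | 13.6% |
| 0.5 | 0.5 | 24.7% | 12.6% |
| 0.5 | 0.7 | 21.9% | 12.6% |
| 0.7 | 0.7 | 19.1% | 10.9% |
| 0.8 | 0.9 | 14.0% | 9.8% |

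As a check on the simulation, the six post-baseline contrasts without the average give 26.5% at zero correlations, which matches the formula. If each contrast is instead a change from baseline, the rate is 23–26% for between-score correlations of 0–0.5 and about 18% at 0.8.

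**The average.** With no effect at baseline and a constant effect δ at both later times, the three-time average estimates (0 + δ + δ)/3 = 2δ/3.

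**Cost of Holm over three scores.** The first step tests at 0.05/3 = 0.0167, so the critical value rises from 1.960 to 2.394. At 80% power the detectable difference grows by (2.394 + 0.842)/(1.960 + 0.842) = 3.236/2.802 = 1.155, about 15%.

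**The case against.** The strongest reply is that the error rate belongs to a decision rule the document does not contain. The article says outcomes are assessed at each time. It does not say that one significant result is enough, sets no test level for KAP, and does not say that p-values go unadjusted. A multiplicity rule may sit in a statistical analysis plan that is not shown, so its absence here is no finding. A rule requiring all three scores to succeed at one fixed time would keep the error at or below 5%. This stands, and it is why every percentage above is conditional.

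A reader might infer that following the plan produces a definite false-positive rate of about a third, or 37% from nine independent tests. The document does not support that. The 33% end needs zero correlation between related scores and between repeated measures on the same pupils, which is implausible. Nine is also only one count: the GEE description is compatible with a single group-by-time test per score, which makes three tests.

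A reader might further infer that unfavourable results could be left out. The article commits to assessing every time point and the average, and to CONSORT reporting, so this does not follow either. What stays open is which result would be called primary.

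None of this removes the core point. Which score and time are primary defines the trial's question and belongs in the section headed Primary outcome. That section goes into detail as fine as the number of reverse-coded items, yet singles out neither.

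**Conclusion.** The point holds in a limited form. The protocol article fixes neither a primary KAP score nor a primary time, and its stated scheme gives several contrasts equal rank. Under an any-contrast rule with unadjusted 0.05 tests, which is an assumption, the nominal family-wise error is roughly 14–33% with the document's own three-time average, and about 22–25% at a between-score correlation of 0.5 and between-time correlations of 0.5–0.7. With one test per score it is about 10–14%. No any-contrast setting examined comes near 5%. These are nominal rates: with two schools per arm, each GEE test may itself exceed 5%. Separately, the three-time average dilutes a constant post-baseline effect to two thirds. This should be corrected, and it can be done with a small change of wording.

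**What to change.** In the Primary outcome and Statistical analysis sections, and in the matching sentence of the Abstract:

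- Name one post-baseline time for the primary between-group contrast, for example the post-intervention assessment.
- Test the three KAP scores at that time with Holm's procedure at a family-wise 5% (ordered p-values against 0.0167, 0.025 and 0.05). Alternatively, name one lead score, test it at 0.05 and make the other two secondary.
- Label the other post-baseline time and the average over times as secondary.

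The cost is a few sentences of analysis wording. Holm raises the detectable difference for a single score by about 15% at its first step. Naming a lead score avoids that loss but gives up primary claims on the other two. Neither option secures a true 5% by itself: Holm holds its level only if each cluster-adjusted GEE test is valid, which two schools per arm do not assure.

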## Materials and methods

### Study design

The cluster randomized controlled trial (RCT), employed for this study, is considered a formidable technique, when it comes to the management of the subject’s characteristics, and threats to its internal validity [22]. A cluster randomized controlled trial design is frequently employed in health intervention research, as it compares individuals connected to specific institutions. Assessments are conducted at baseline, post-intervention, and during follow-up after two months, as shown in Fig 1 [23].

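### Good knowledge, within the primary outcome, is defined as scoring above an unspecified mean; if that mean is recomputed at each visit, within-arm change is distorted

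*Protocol article*

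**What the plan says.** Under Primary outcome, the KAP-Q is used "to measure the primary outcome of interest for this study". Its knowledge section has 30 items, each scored 1 if correct and 0 otherwise: "The maximum score is 30, and the minimum 0". The article then adds: "A score above the mean is an indication of good knowledge".

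The other two sections of the questionnaire get a direction and no cut. For attitude the text is "A higher score is an indication of a greater positive attitude", and for practice "A higher score is an indication of a more positive practice".

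Study design sets three measurement times: "Assessments are conducted at baseline, post-intervention, and during follow-up after two months". Statistical analysis applies GEE to the selected outcomes, between and within groups, and states: "Outcomes will be assessed at each time point, along with derived average overall three-time points". The same section says of variables that fail the normality check: "Data not normally distributed, will be transformed into a categorical variable". It names no cut for that step. It also assigns Friedman's test to within-group change when data are not normal.

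**The concern.** A threshold used to judge change must stay still while the scores move. This one is tied to a mean that the article does not identify. The programme is meant to raise knowledge, so any mean taken from scores observed after it starts will rise with the programme. The proportion above that mean then says where a pupil stands among peers at that visit. It does not say whether knowledge improved.

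The other cut-points stated for outcomes are numbers: 2.33 and 3.66 on the PAQ-C, 4 hours a day on the ASAQ, 20 on the EAT-26, and the BMI limits. The relative cut sits in the primary outcome.

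At stake are statements about change over time within each arm, which the plan intends to make. A control arm that had not changed could be reported as losing knowledge, and a shared gain (for example from answering the same questionnaire again) could be reported as none.

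**Working it through.** **The plan's own figure.** There is none to reproduce on this point. The sample size rests on proportions overweight and does not involve the knowledge score.

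**Inputs from the article.** Score range 0-30; three visits; 125 pupils per arm, so equal arms; a cut at an unidentified mean.

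**Assumptions, because the article gives no values.** Scores are normal with a common SD, and the arms have equal means at baseline. The main case is a 0.5 SD gain in the intervention arm and none in control.

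**Formula.** Proportion with good knowledge = Φ((arm mean − cut) / SD). Measure in SD units from the baseline mean, so that after the programme the intervention mean is 0.5 and the control mean is 0. At baseline every version of the cut gives 50% in both arms.

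| Which mean is the cut | Cut | Intervention | Control | Difference | Odds ratio |
|---|---|---|---|---|---|
| Pooled baseline mean, frozen | 0 | Φ(0.5) = 69.1% | Φ(0) = 50.0% | 19.1 points | 2.24 |
| Pooled mean at the visit | 0.25 | Φ(0.25) = 59.9% | Φ(−0.25) = 40.1% | 19.7 points | 2.23 |
| Each arm's own mean at the visit | 0.5 and 0 | Φ(0) = 50.0% | Φ(0) = 50.0% | 0 | 1.00 |

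(The 19.7 is 59.87 − 40.13 before rounding.)

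**Within-arm reading, pooled mean at the visit.** Control goes from 50% to 40%, an apparent loss of 10 points with no change in its scores. Intervention goes from 50% to 60%, where the frozen cut shows 50% to 69%.

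**Shared gain.** If both arms gain 0.5 SD, the pooled cut moves to 0.5 and both arms stay at Φ(0) = 50%. The frozen cut shows 50% to 69% in both. The between-arm difference is zero either way, which is right.

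**Range in score points.** With an SD of 3.5 to 6 and an intervention-only gain of 2 to 6 points:
- Pooled mean at the visit: the unchanged control arm appears to fall to between 43% and 20%.
- Frozen cut: control stays at 50% and intervention reaches 63% to 96%.
- Between-arm odds ratio at SD 4.5 and a 4-point gain: 4.18 pooled against 4.35 frozen. In the most extreme case (SD 3.5, gain 6) it is 16.89 against 22.13.

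A simulation of whole-number scores, 125 per arm, with SD 4.5 and a gain of 4 points agrees with the formula: 67.3% and 32.9% (pooled), 50.1% and 50.0% (arm-specific), 81.2% and 50.0% (frozen).

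**How readily a category could be called for.** I drew normal scores with an assumed mean of 16, rounded them to whole points, and applied the Kolmogorov-Smirnov test in its Lilliefors form at 0.05 (500 runs per setting). With 250 pupils it rejected normality in about 99% or more of runs at SD 3.5, 87% at SD 4.5 and 54% at SD 6. With 125 pupils the figures were about 68%, 45% and 25%. Whole-point scoring alone can therefore trigger the rule. This is a likelihood, not a certainty, because the article also lists a skewness and kurtosis check and does not say which prevails.

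**The case against.** The strongest objection is that the article does not say the cut moves. It says only the mean. A baseline mean frozen for all visits fits the sentence as well and produces no artefact. The questionnaire also follows two cited studies whose method for the cut is not shown. This stands: the documents support an unspecified cut, not a cut known to be recomputed.

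Second, the sentence may be only a gloss on what a score means. The 0-30 score is fully defined, and nowhere is the percentage with good knowledge named as an analysed endpoint. This stands in part. The conversion rule for non-normal data gives a category a stated route into the analysis, and no other category for knowledge is supplied.

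Third, Friedman's test ranks the scores and needs no cut, so not every within-group statement would be affected. This also stands, but the GEE is meant to test within-group effects too, and the article does not reconcile Friedman's test with the instruction to categorise.

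A reader might go further and infer that a real programme effect would disappear from the trial's main comparison. The documents do not support that. It would need a separate mean for each arm, which nothing in the text suggests. With a pooled mean the randomised contrast at a visit is almost unchanged at 0.5 SD.

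**Conclusion.** The concern holds in a limited form. The only classification of knowledge within the primary outcome rests on an unidentified mean, and the plan's rule for non-normal data can bring that classification into the analysis. If a pooled mean is recomputed at each visit, within-arm change is misreported: at an assumed 0.5 SD gain in one arm, an unchanged control arm appears to lose 10 percentage points, and a gain common to both arms is hidden. The between-arm contrast largely survives (odds ratio about 2.23 against 2.24).

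The percentages rest on normal scores, equal arms with equal baseline means, and assumed gains and SDs. There is no harm if the 0-30 score is what is analysed and reported, or if the mean is frozen at baseline. The article commits to neither. It deserves correction before follow-up data are seen, because the apparent result depends on a choice that could otherwise be made afterwards.

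**What to change.** State that knowledge is analysed in the GEE as the 0-30 score, and that it is not dichotomised if it fails a normality check.

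If a good-knowledge percentage is also to be reported, replace the mean rule with one cut used at every visit and in both arms. Either of these would serve:
- the pooled baseline mean, calculated once and frozen before any follow-up data are seen; or
- a prespecified number of correct answers out of 30.

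The cost is a sentence in the outcome definition and a matching exception in the Statistical analysis section. No new data, visits or pupils are needed.
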